## Abstract

**Introduction:**

Young smokers always partake in both smoking and drinking. However, drinking undermines their likelihood to attempt quitting smoking or to successfully abstain from smoking. Hence, this trial will examine the feasibility of implementing an integrated smoking cessation and alcohol intervention in young Hong Kong Chinese people. Effect sizes of the integrated intervention (II) on self-reported and biochemically validated quit rates will also be calculated.

**Methods:**

The study will be a three-arm randomized controlled trial in a convenience sample of 150 smokers aged 18–25 years with alcohol drinking. Participants will be randomized into a standard treatment (ST), II, or control arm. The ST group will receive a brief smoking cessation intervention based on the 5A (Ask, Assess, Advice, Assist, Arrange) and 5R (Relevance, Risks, Rewards, Roadblocks, Repetition) models. The II group will receive brief advice on alcohol use based on the FRAMES (Feedback, Responsibility, Advice, Menu, Empathy, Efficacy) model in addition to the brief smoking cessation intervention. Both the ST and II groups will receive booster interventions at 1-week, 1-month, 3-month, and 6-month follow-up. The control group will receive leaflets on smoking cessation and alcohol reduction. Self-reported quitters at 6-month follow-up will be invited for biochemical validation. The primary outcomes are feasibility measures. The secondary outcomes are effect size of II on self-reported and biochemically validated quit rates at 6 months relative to control and ST. Outcomes will be assessed at baseline and at 1-week, 1-month, 3-month, and 6-month follow-ups.

**Analysis:**

Descriptive statistics will be used to calculate the feasibility measures. The three arms will be compared using analysis of variance for continuous variables and chi-square test for categorical variables. Effect sizes of II for self-reported and biochemically validated quit rates at 6 months will be determined using the generalized estimating equation model.

## Trial registration

**Trial registration number:**
NCT05627765.

## Introduction

Cigarette smoking is a major public health concern. It remains the single most preventable cause of death [1]. Evidence has shown that smoking damages nearly every organ in the body [1] and is associated with numerous chronic diseases [1]. Recent evidence has indicated that smoking is the cause of death in two out of three smokers, especially when smoking is initiated at a young age [2,3]. Therefore, it is paramount to actively promote smoking cessation among young smokers to reduce smoking-attributable diseases and mortality in this population.

Evidence has shown that young smokers always partake in both smoking and drinking [4,5]. A national survey in the United States showed half of the people aged 12 or older (51.1 percent) drank alcohol in the past month and 1 in 5 (21.5 percent) used a tobacco product [6]. Moreover, alcohol use has been found to be highly related to cigarette smoking [7]. A previous study indicated that smokers were 1.32 times more likely to drink than non-smokers [7]. Another study found that smoking prevalence was 75% higher among drinkers compared with non-drinkers [8]. Alcohol use has been well-recognized as a high-risk situation that precipitates cigarette cravings and relapse [8]. One study showed that drinkers were less likely to attempt quitting and to succeed in quitting compared with non-drinkers [8].

Although a considerable number of young smokers are drinkers, current smoking cessation interventions are focused only on smoking behaviors, and alcohol drinking are generally overlooked [4]. In fact, drinking combined with smoking can lead to numerous health conditions. For example, concurrent heavy use of tobacco and alcohol can have a significant impact on the development of malignancies [7,8]. Exposure to tobacco and alcohol also results in multiplicative risk for heart attack, heart failure, stroke, gastric problems, liver cirrhosis, pancreatitis and memory loss [7]. Britton et al. [9] suggested that smoking cessation interventions that target smokers with alcohol drinking is ideal because of their significant risk for negative health and poor cessation outcomes. Therefore, an intervention that combines smoking cessation and alcohol reduction will substantially improve the physical well-being of young smokers with alcohol drinking. Furthermore, such interventions will enhance abstinence because drinking undermines the likelihood of quitting smoking and increases the chance of relapse [8].

A literature search has identified some studies that investigated integrated interventions [10–13]. For example, one pilot study evaluated the acceptability of an integrated smoking cessation and drinking intervention in young adults [10]. A total of 41 young adult smokers who were regular drinkers were randomly assigned to either the standard treatment (eight individual-based counseling sessions plus 8 weeks of nicotine patch therapy) or integrated intervention. Results demonstrated that the integrated intervention was highly acceptable to young smokers. Furthermore, young smokers who received the integrated intervention reported higher biochemically validated quit rates than those who received the standard treatment. Another study was a two-arm randomized controlled trial (RCT) comparing the efficacy of a technology-based integrated smoking cessation and alcohol intervention and a smoking cessation only intervention in adolescents [11]. A total of 1471 participants were randomized into one of the interventions and results indicated that the integrated intervention exhibited no advantages of self-reported quit rates over the smoking cessation only intervention.

Although these studies addressed the effectiveness of integrated smoking cessation and alcohol interventions, they had limitations that warrant further investigation. The study by Ames et al. [10] did not use intention-to-treat to handle missing data, leading to an overestimation of the intervention effect. Despite promising findings, the results were not statistically significant because of an insufficient sample size. In the study by Haug et al. [11], participants’ smoking status was not biochemically verified, which may have led to an overestimation of intervention effectiveness because of social desirability bias. Moreover, the study did not have a control group, precluding conclusions regarding absolute intervention effectiveness. Third and perhaps most importantly, some participants did not have alcohol drinking and therefore, an integrated intervention is less relevant to these individuals, weakening the intervention effectiveness and contributing to the non-significant findings. Because of these limitations, re-examining the effectiveness of integrated smoking cessation and alcohol interventions in young smokers in a large-scale RCT is imperative. Our pilot study will be an important prerequisite to ensure feasibility of implementing such interventions in the Hong Kong Chinese context.

The study’s research questions are:

What is the feasibility of an integrated smoking cessation and alcohol interventions in young smokers?Will the use of an integrated smoking cessation and alcohol interventions be more effective to help young smokers achieve abstinence compared with interventions that are focused on smoking cessation alone?

### Theoretical framework

The relationship between smoking and drinking can be explained by classical conditioning [14], where the unconditioned stimulus is a stimulus that triggers an unlearned natural response. A neutral stimulus is a stimulus that produces no specific response. For example, food (unconditioned stimulus) triggers salivation in dogs (natural response), but a ringing bell (neutral stimulus) does not. However, repeated exposure to a natural stimulus that is followed by unconditioned stimulus leads to the two stimuli becoming paired. Eventually, the natural stimulus becomes a conditioned stimulus that serves as a signal for the unconditioned response (e.g., the ringing bell [conditioned stimulus] triggers salivation in the dogs [conditioned response]) [14]. This theory has been applied extensively to the relationship between drinking and smoking. Specifically, the frequent pairing of alcohol and cigarettes results in alcohol serving as a conditioned stimulus that triggers a conditioned response of cigarette craving, which increases lapse and relapse [14].

Another explanation for the relationship is reduced cognitive capacity [14]. It has been postulated that alcohol consumption creates a supportive environment for smoking, whereby drinking impairs cognitive function and reduces the amount of information that can be processed. This leads to disinhibition and engagement in risky behavior, such as smoking. Moreover, because of the impairment in cognitive function, people suppress thoughts that smoking is harmful to their health. Additionally, the contextual environment that drinking takes place often involves smokers, which can increase an individual’s motivation to smoke [14].

Standard treatment based on the ‘5A’ and ‘5R’ models proposed by the World Health Organization is recommended as a common smoking cessation intervention [15–20]. This was chosen as a comparator because we wanted to determine whether II is more effective than the current smoking cessation practice. Additionally, usual care, i.e., leaflet related to smoking cessation and alcohol drinking, was also chosen as another comparator because it only has minimal effect on smoking cessation outcomes [21]. This could maximize the comparison to show the intervention effect of II. We hypothesize that an integrated smoking cessation and alcohol intervention that aims to cease both behaviors will be more effective in helping young smokers to achieve self-reported and biochemically validated abstinence at 6 months compared with the standard treatment based on the ‘5A’ and ‘5R’ models and the control that is receiving leaflets related to smoking cessation and alcohol drinking. This hypnosis is based on our reasoning that the II will remove smokers from drinking environments that support smoking and eliminate smoking cues. As such, we will conduct a 3-arm (1:1:1), superior, parallel, non-blind, randomized controlled trial to test the feasibility and preliminary effectiveness of integrated smoking cessation and alcohol interventions in young Hong Kong Chinese smokers.

## Materials and methods

### Study design and objectives

We will conduct a three-arm RCT to examine the feasibility of implementing an integrated smoking cessation and alcohol reduction intervention in young Hong Kong Chinese smokers. The three arms will be standard treatment (ST), integrated smoking cessation and alcohol intervention (II), and control. We will assess the feasibility of the intervention based on screening rate, eligibility rate, recruitment rate, randomization rate, attendance rate of intervention, adherence to intervention protocol, retention rate, completion rate, missing data, and adverse events. In addition, we will calculate the effect size of II based on biochemically validated and self-reported quit rates at 6 months. According to previous literature [10,11], our intervention is expected to achieve at least a small effect size relative to ST and control. Fig 1 shows the CONSORT diagram.

**Fig 1 pone.0289633.g001:**
[figure not shown]
CONSORT diagram.

### Sample

Individuals are eligible for the study if they are (1) aged 18 to 25 years, (2) smoked at least one cigarette in the past 30 days, (3) consumed at least one cup of alcohol (10 ounces of beer, 4 ounces of wine, or 1 ounce of liquor) [4] in the past 30 days, and (4) speak Cantonese. Exclusion criteria include: (1) have cognition and/or communication problems, (2) have clinically reported mental disorders (anxiety, depression, etc.), (3) current use of nicotine containing medication, (4) participating in other smoking cessation interventions including pharmacological interventions. We will target participants aged 18–25 years because this age range is considered young adulthood [22]. Smokers aged <18 may also have alcohol drinking; however, their psychosocial development differs from those who reach the age of majority [23]. Therefore, we only targeted those aged 18–25 years to ensure the homogeneity. As this study aims to explore the feasibility and preliminary effect of II on smoking cessation among young smokers, we do not set any restriction on nicotine dependency. Hence, light and heavy smokers will be included. This variable will also be controlled in our GEE model. However, non-smokers will not be included. Similarly, we will not set any restriction on the participants’ alcohol dependency. However, participants will be categorized as heavy drinkers when exceeding the following threshold: drinking on a maximum of 5 days per week, maximum 3 glasses per day and 14 per week for women, and maximum five glasses per day and 21 per week for men [24]. This variable will also be controlled in the GEE model. According to Department of Health, Hong Kong [25], regular drinkers are defined as those who drink at least once in 7 days, whereas occasional drinkers are those who drink once in 30 days. We will include occasional drinkers because occasional drinking can also lead to smoking lapses and relapses [4].

There is no fixed rule for calculating sample size for a pilot study [26]. Based on the sample size estimation guide for pilot studies outlined by Birkett and Day [27]. 50 participants per arm will provide 80% power to detect differences between the groups, assuming a 5% alpha error and a 10% attrition rate. Hence, a total of 150 participants will be recruited for this study.

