### Intervention

Standard treatment (ST) arm

Participants will receive a brief smoking cessation intervention based on the ‘5A’ and ‘5R’ models proposed by the World Health Organization. The ‘5A’ model emphasizes five steps: ***A***sking about tobacco use, ***A***dvising smokers to quit, ***A***ssessing their willingness to quit, ***A***ssisting in quitting, and ***A***rranging for follow-up [8]. Accordingly, our trained research assistant (RA) will ask participants about their tobacco use. The RA will then advise them to quit by a strong message: ‘*According to the World Health Organization*, *smoking kills one in every two smokers*. *Quitting smoking is important to protect your health*. *We are here to help you*.*’* The RA will then assess their willingness to quit by asking two questions: *‘Would you like to quit smoking*?*’* and *‘Do you think you can quit smoking successfully*?*’* If the participant replies *‘yes’* to the first question and either *‘yes’* or *‘unsure’* to the second question, they will be considered smokers who are ready to quit, and the RA will assist them to quit using the **STAR** method: ***S***et a quit date within 1 week, ***T***ell people around them about the participant quitting and solicit support, ***A***nticipate challenges to quit attempt, and ***R***emove all tobacco products. Participants who reply either *‘unsure’* or *‘no’* to the first question and *‘no’* to the second question will be considered smokers who are not yet ready to quit and the ‘5R’ model will be applied. This model comprises five components: ***R***elevance, ***R***isks, ***R***ewards, ***R***oadblocks and ***R***epetition. Accordingly, the RA will ask participants to think about how quitting smoking is personally relevant and encourage them to identify the potential risks of smoking and potential rewards of quitting. The RA will then guide participants to think about any roadblocks to quitting and provide corresponding solutions. Finally, the RA will repeat the assessment of their willingness to quit. Lastly, the RA will arrange follow-up with the participants by phone.

Booster intervention

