#### Control arm

Participants will be provided with two leaflets designed by Department of Health, Hong Kong, with one for smoking cessation and another for alcohol reduction, and scheduled telephone follow-up similar to the ST group. They will receive the placebo intervention and boosters of the same duration, promoting their fruit and vegetable intake. According to Li et al. [20], this placebo intervention and boosters do not have any intervention effect on the smoking-related outcomes.

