### Outcome

The primary outcomes are feasibility measures: screening rate, eligibility rate, consent rate, randomization rate, attendance rate of intervention, adherence to intervention protocol, retention rate, completion rate, missing data, and adverse events. The secondary outcomes are effect size of II on self-reported and biochemically validated quit rates at 6 months relative to control and ST. These quit rates are the most useful outcomes to show the effectiveness of smoking cessation interventions [21]. Six months was chosen because it is the gold standard follow-up duration for evaluation in smoking cessation trials [4,15–20,31].

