### Measurements

Feasibility measures include screening rate (the number of eligible smokers divided by the number of screened people), eligibility rate (the number of eligible smokers divided by the number of screened people), consent rate (the number of eligible smokers who agree to participate divided by the number of eligible smokers), randomization rate (the number of participants who are randomized divided by the number of eligible smokers who consent to participate), attendance rate(the number of participants who complete the intervention divided by the number of participants who are randomized into the treatment arms (ST and II)), adherence to intervention (the number of participants in the two treatment arms who practice the skills learned during the intervention divided by the number of participants in the two treatment arms), retention rate (the number of participants who remain in the study divided by the number of participants randomized), completion rate (the number of participants who complete the questionnaire divided by the number of questionnaires distributed), missing data (the percentage of missing data), and adverse events (unfavorable or unintended events during the study period that were not present at baseline or appear to have worsened since baseline [32]).

The proposed secondary trial outcome is effect size of II on self-reported and biochemically validated quit rates at 6 months relative to control and ST. The self-reported quit rate will be measured using a structured questionnaire designed by our team. The questionnaire will cover six areas: smoking profile (i.e., number of cigarettes smoked per day, age when starting to smoke, years of smoking, and the Fagerstrom test, which is the gold standard test for physical dependence on nicotine) [15–20,31], cessation history (i.e., previous quit attempts, when previous quit attempt was initiated, and duration of abstinence), readiness to quit, self-efficacy to quit, alcohol use, and demographics. Besides the items measuring the fact of participants, which are not possible to have the psychometric properties, the construct reliability coefficient for the Fagerstom test was 0.74 [33]. and the Cronbach’s alpha for measuring alcohol use using the Alcohol Abstinence Self-Efficacy Scale (AASE) was 0.98 [34]. The biochemically validated quit rate will be confirmed by measuring the level of carbon monoxide in expired air (< 4 ppm) and level of cotinine in saliva (< 115 ng/mL) [15–20,31].

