### Data collection

Participants will be recruited from smoking hotspots in Mong Kok. Smoking hotspots are places where many smokers congregate [31]. Mong Kok is one of the most popular places among Hong Kong youth, including young smokers [35]. The RA will approach smokers who smoke in selected smoking hotspots to deliver leaflets containing information of the study. If smokers are willing to participate, the RA will check their eligibility. Eligible smokers will be invited to join. For smokers who are ineligible or refuse participation, the RA will remind them of the health effects of smoking and drinking and refer them to the government’s quit line. The timeline of this study was presented in S2 File.

Data will be collected at baseline, 1 week, 1 month, 3 months, and 6 months, which are data collection timepoints that are commonly used in smoking cessation trials [4,19,20,31]. All participants will complete a structured questionnaire at each timepoints via telephone. Self-reported quitters at 6 months will be invited for biochemical validation.

Participants in the II arm with high (80%–100%) and low (0%–20%) adherence will be purposively selected for one-to-one, 20–30 minutes, semi-structured interviews to further assess the feasibility of II. All interviews will be conducted by the RA in a meeting room of a local university following a semi-structured interview guide and will be audio recorded. Sample size will be determined by data saturation. Based on previous smoking cessation studies [4,16], we expect data saturation to occur after interviewing 30 participants: 15 from the high adherence group and 15 from the low adherence group. As one outcome of this study is to test the feasibility of the II, no incentive will be provided to the participants.

The audit will be conducted by one auditor who was blinded to experimental or control sites. She will regularly audit the overall quality and completeness of the data, examine source documents, interview investigators and coordinators, and confirm that the clinical center has complied with the requirements of the protocol.

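### The two-marker validation rule makes no provision for nicotine medication started after entry, so a true quitter using it at the 6-month sample can be scored as not validated

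*Protocol article*

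**What the plan says.** The Sample section of the protocol article gives, as its third and fourth exclusion criteria, "3) current use of nicotine containing medication, (4) participating in other smoking cessation interventions including pharmacological interventions". Both are worded as conditions at screening.

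The Measurements section confirms a validated quit by "measuring the level of carbon monoxide in expired air (< 4 ppm) and level of cotinine in saliva (< 115 ng/mL" in combination, and states no exception. The Data collection section limits who is tested: "Self-reported quitters at 6 months will be invited for biochemical validation".

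The Outcome section gives the endpoint its rank: "The secondary outcomes are effect size of II on self-reported and biochemically validated quit rates at 6 months relative to control and ST". The primary outcomes are the feasibility measures.

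The questionnaire is described in Measurements as covering six areas. The areas after the smoking profile are given as "cessation history (i.e., previous quit attempts, when previous quit attempt was initiated, and duration of abstinence), readiness to quit, self-efficacy to quit, alcohol use, and", with the participant's background as the sixth. Cessation aids taken up during follow-up are not named. The article does not say how nicotine medication or other cessation help begun after entry is recorded or classified.

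**The concern.** The entry criteria show that the sponsor regarded outside nicotine treatment as relevant to the comparison, but they act on one day only. Participants in the standard treatment (ST) and integrated intervention (II) arms who are ready to quit are then helped to set a quit date within a week, and telephone boosters continue to 6 months. The sample has no restriction on nicotine dependency, so heavy smokers are included. That some participants will obtain nicotine medication on their own is foreseeable.

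CO is a marker of smoke and cotinine a marker of nicotine. Someone who has stopped cigarettes with the help of nicotine medication can pass the first and fail the second. The rule as written then withholds validation from a true quitter. Validated quitting at 6 months is one of the two effect sizes that the trial is to deliver, and the Discussion plans a full-scale trial on its results.

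**Working it through.** The plan gives no quit rates and no expected use of nicotine medication, so it has no figure of its own to reproduce here. The check has two parts.

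**1. The rule applied to possible cases.** Among self-reported quitters tested at 6 months:

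| Participant | CO < 4 ppm | Cotinine < 115 ng/mL | Validated? |
|---|---|---|---|
| Smoke-free, no nicotine product | yes | yes | yes |
| Smoke-free, nicotine medication that ended well before the sample | yes | yes | yes |
| Smoke-free, nicotine medication at the sample, cotinine below the limit | yes | yes | yes |
| Smoke-free, nicotine medication at the sample, cotinine at or above the limit | yes | no | no |

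Only the last row is misclassified. Failure needs both use close to the 6-month sample and a cotinine level at or above the limit.

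**2. Effect on the validated quit rate.**

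Input from the documents: 50 participants per arm (Sample).

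Assumptions, not in the documents: true quit rates of 10% in control and 20% in II, and a loss fraction *L* between 0 and 0.20 in each arm. *L* = (share of true quitters using nicotine medication at the sample) × (share of those with cotinine at or above 115 ng/mL).

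Formula: observed validated rate = true quit rate × (1 − *L*).

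| *L* control | *L* II | Control | II | Risk difference (points) | Risk ratio | Odds ratio |
|---|---|---|---|---|---|---|
| 0 | 0 | 10% | 20% | 10 | 2.00 | 2.25 |
| 0.10 | 0.10 | 9% | 18% | 9 | 2.00 | 2.22 |
| 0.20 | 0.20 | 8% | 16% | 8 | 2.00 | 2.19 |
| 0 | 0.20 | 10% | 16% | 6 | 1.60 | 1.71 |
| 0.20 | 0 | 8% | 20% | 12 | 2.50 | 2.88 |

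Example, fourth row: II 0.20 × (1 − 0.20) = 0.16; difference 0.16 − 0.10 = 0.06; ratio 0.16 / 0.10 = 1.60; odds ratio (0.16/0.84) / (0.10/0.90) = 1.71.

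In people, the largest losses are 50 × 0.20 × 0.20 = 2 quitters in II and 50 × 0.10 × 0.20 = 1 in control. Each one moves an arm's rate by 1/50 = 2 points.

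Equal loss lowers both rates, leaves the risk ratio unchanged, and shrinks the risk difference and, slightly, the odds ratio. Unequal loss distorts the risk ratio in either direction. With assumed true rates of 5% and 15% the pattern is the same: a risk ratio of 3.00 becomes 2.40 if *L* is 0 in control and 0.20 in II, and 3.75 if reversed. If the true rates are equal at 10%, unequal loss of this size creates a spurious difference of 2 points, in either direction.

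**The case against.** **The article condenses a fuller document.** Rules for concomitant cessation aids may stand in the full protocol, the case forms or the analysis plan, and the article lists questionnaire areas, not items. This stands in part, and it weakens any claim that the data will not be collected. It does not remove the point, because the outcome rule is stated with its thresholds and its joint requirement, and that rule misclassifies a foreseeable case.

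**Requiring both markers is a defensible, conservative choice.** This stands as a reason to keep the two-marker result. It is not a reason to leave the classification of nicotine-medication users unstated.

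**Discordant results would be visible.** CO and cotinine are separate measurements, so anyone with low CO and high cotinine could be counted afterwards. This stands. What may be missing is the reason: discordance alone does not separate nicotine medication from smoking that CO failed to detect.

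**Stronger readings that the documents do not support.**

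- A reader might infer that the loss falls mainly on the active arms. No arm is described as supplying nicotine medication. Control also receives a cessation leaflet, and its calls are matched in length: "They will receive the placebo intervention and boosters of the same duration, promoting their fruit and vegetable intake". Control participants, without counselling, might seek outside help more often. II and ST share the same cessation advice, so cessation counselling gives little reason to expect different use between those two.
- A reader might take the fall from 10 to 6 points in the table, a 40% loss, as an estimate. It needs two of ten II quitters affected and none in control. Those counts are assumed, and the loss may be nil.
- A reader might infer that cotinine is required from every participant. Only self-reported quitters are invited.
- A reader might infer that unrecorded outside help confounds the self-reported effect. Help taken up after randomisation is not a confounder of an intention-to-treat comparison; it is a consequence that may follow from the assigned arm. Leaving it unrecorded limits interpretation only.

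**Conclusion.** The concern holds in a limited form. As stated, the validation rule scores a smoke-free participant as not validated if nicotine medication is in use near the 6-month sample and cotinine is at or above 115 ng/mL. The plan shown neither records such use nor says how to classify it. Validated quit rates are then too low. Whether the effect size is also biased in relative terms depends on a difference in use between arms, about which the documents are silent. Under the assumed 10% and 20% quit rates and losses of 0 to 0.20, the risk difference ranges from 6 to 12 points around a true 10. These are illustrations, not predictions.

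Severity is minor: the rule bears on one secondary outcome of a pilot and touches neither the feasibility outcomes nor the self-reported quit rate. It is still worth settling before follow-up ends, because self-report of aid use cannot be reliably collected later.

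**What to change.** 1. At each follow-up, in all three arms, ask about nicotine-containing medication or products and other cessation help since the last contact. Tabulate the answers by arm.
2. Add to the outcome definition that self-reported quitters who report current non-cigarette nicotine use at 6 months are validated on CO, and report how many are classified this way.
3. Report the validated quit rate and its effect size under both this rule and the two-marker rule applied to all who are tested.

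If a fuller document already covers this, one sentence in the outcome definition that points to it is enough. The proposal concerns recording and classification only, not whether participants may use such medication.

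The cost is one or two telephone questions per contact and a short addition to the outcome definition. The downside is that CO alone is a less sensitive check for smoking in those few participants, which is why both results should be shown.

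### The 80% power claimed for 50 per arm names no endpoint or difference, and it does not fit the only effect size the plan anticipates

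*Protocol article*

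**What the plan says.** The Sample section first notes that pilot studies have no set sample-size rule. It then cites a guide for sizing them, asserts that "50 participants per arm will provide 80% power to detect differences between the groups, assuming a 5% alpha error and a 10% attrition rate", and concludes that "a total of 150 participants will be recruited for this study".

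The only statement about the size of the effect is under Study design and objectives, which rests it on two earlier studies: "our intervention is expected to achieve at least a small effect size relative to ST and control". No number is attached to it, and the Sample section does not refer to it.

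The Outcome section makes feasibility primary. The effect of the integrated intervention (II) on 6-month quit rates, relative to standard treatment (ST) and control, is secondary. The second research question in the Introduction is nevertheless one of effectiveness: "Will the use of an integrated smoking cessation and alcohol interventions be more effective to help young smokers achieve abstinence". The Theoretical framework section hypothesises that II is superior to both comparators.

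**The concern.** Power is defined only for a stated difference on a stated endpoint. The Sample section gives neither, so a reader must look elsewhere for the effect that the 80% refers to. The one candidate is an effect that is at least small, and 50 per arm is far too few to have 80% power at the lower end of that range.

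The practical risk lies in how a result is read. The article poses a superiority question, plans chi-square comparisons of the arms (Data analysis), and says in the Discussion that a full-scale trial will build on the results. With 80% power in print, a non-significant II-versus-ST comparison could pass for informative negative evidence. If the true effect were small, that outcome would be the expected one.

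**Working it through.** **Inputs from the article.** 50 randomised per arm, 1:1:1, 150 in total; 5% alpha, sidedness not given; "a 10% attrition rate"; a binary endpoint (6-month quit rate). Data analysis counts participants lost to follow-up as smokers, so up to 50 per arm may be analysed. Results are therefore shown for 45 and for 50.

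**Assumptions.** Small = 0.2 on the standardised scale (Cohen's h for proportions, d for means). Two-sided 5% unless stated. Comparator quit rates of 5% to 20%, because the article gives none.

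**1. The plan's own figure.** The attrition step is consistent: 50 × 0.90 = 45. The 80% cannot be reproduced, because no difference is given.

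**2. Effect that gives 80% power.** h = (1.960 + 0.842) × √(2/n).
- n = 45: 2.802 × 0.2108 = 0.59
- n = 50: 2.802 × 0.2000 = 0.56

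In quit rates, by the pooled-variance formula for two proportions with 45 per arm, this is 5% against 26%, 10% against 34%, or 20% against 48%. That formula gives slightly larger effects than the approximation above: h of about 0.62, 0.60 and 0.60.

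**3. Power at 0.2.** Power = Φ(0.2 × √(n/2) − z).

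| | 45 per arm | 50 per arm |
|---|---|---|
| Two-sided 5% | Φ(0.949 − 1.960) = 15.6% | Φ(1.000 − 1.960) = 16.9% |
| One-sided 5% | Φ(0.949 − 1.645) = 24.3% | Φ(1.000 − 1.645) = 26.0% |
| Two-sided, Bonferroni for two comparisons | 9.8% | 10.7% |
| Two proportions at h = 0.2, comparator 5% to 20% | 15.1% to 15.4% | 16.4% to 16.6% |
| Three-arm F or chi-square test, f or w = 0.1 | 16.2% to 16.4% | 17.6% to 17.8% |

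At a comparator rate of 10%, h = 0.2 means 10% against 16.8%.

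**4. Sample size for 80% power at 0.2.** n = 2 × 2.802² / 0.2² = 392.6, rounded up to 393 analysed per arm. 393 / 0.90 = 436.7, rounded up to 437 randomised per arm.

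**5. Could an unstated medium effect explain the 80%?** With no attrition it comes close: 78.8% for a three-arm chi-square test (w = 0.25), 78.0% for analysis of variance (f = 0.25), and 80.4% for a one-sided comparison (d = 0.5). With 45 per arm these fall to 74%, 73% and 77%.

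**6. What 150 does provide.** Wilson 95% intervals at an assumed feasibility proportion of 80%:
- one arm, 40/50: 67.0% to 88.8%
- all participants, 120/150: 72.9% to 85.6%

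For the quit-rate difference at 10% against 16.8% with 50 per arm, the 95% half-width is 1.96 × √[(0.10 × 0.90 + 0.168 × 0.832)/50] = 1.96 × 0.0678 = 0.133. That is about ±13 percentage points around a difference of 6.8 points.

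**The case against.** The strongest reply is that the 80% has not been shown to be false. Without an effect size it is unverifiable, and the Sample section ties it to a cited guide that is not at hand, not to the small effect mentioned elsewhere. This stands. A reader might infer that the design is proven not to have its stated power. The article does not support that, since some larger, unnamed effect would give 80%. What can be said is that the figure has no stated basis and does not fit the lower end of the one expectation the article offers.

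It also stands that 0.2 and two-sided testing are conventions, and that the expectation is of an effect at least small, so 16% is power at the floor. One-sided testing raises it only to 24% to 26%.

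A further reply is that this is a pilot with feasibility as its primary outcome. That is a good reason to keep 150, and it limits the weight of the point. It does not supply a basis for a printed power figure.

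A reader might also infer that the two cited studies give no ground for expecting any effect, since for one of them "the integrated intervention exhibited no advantages of self-reported quit rates over the smoking cessation only intervention". The Introduction does not bear that out. It reports higher validated quit rates with the integrated intervention in the 41-person pilot. It also attributes the other study's null result partly to participants who did not drink, whom this trial excludes. The statement about the expected effect need not be withdrawn on this ground.

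**Conclusion.** The point holds as an unsupported power statement, and it should be corrected. The 80% cannot be derived from the article. At a conventional small effect, no test variant examined exceeds 26%, and two-sided 5% tests without a multiplicity adjustment give 15% to 18%. At the two-sided 5% level, 80% power needs an effect of about 0.59 with 45 analysed per arm, or 0.56 with 50. The article anticipates nothing specific of that size.

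The conclusion rests on reading small as 0.2 and, for the quit-rate examples, on assumed comparator rates of 5% to 20%. Power at h = 0.2 hardly changes over that range. The finding does not show that 150 is the wrong size for a feasibility trial, and it leaves the primary outcomes untouched.

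**What to change.** Keep 150 participants and make three changes of wording.

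1. In Sample, delete the 80% power sentence. Alternatively, restate it with its endpoint, sidedness and detectable effect (about 0.59 with 45 per arm, two-sided 5%), and add that power is about 16% at h = 0.2.
2. Justify the size by the precision of the primary feasibility measures, for example 67% to 89% in one arm of 50 and 73% to 86% in all 150 at an assumed proportion of 80%.
3. In Data analysis, say that the II-ST and II-control quit-rate differences will be reported as estimates with 95% confidence intervals, and that a non-significant result will not be read as evidence of no effect.

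The cost is protocol text only. No participants, visits or data items are added. The stated power becomes less favourable, which matters little where feasibility is primary.
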